#### 2.2.2. Exclusion Criteria

secondary ACLR;ACLR with the use of a method other than autologous ipsilateral semitendinosus tendon graft;diagnosed additional systematic diseases;current impaired performance due to previous injuries apart from the ACL injury;current permanent knee pain or swelling.

### 2.3. Procedure

The examination is performed in a single session, including three runs of the modified BIA test battery.

The patients are asked to abstain from unaccustomed strenuous exercise for at least 24 h before the testing and avoid eating a heavy breakfast in the morning before the test and no rich meals within two hours of the test. They are advised to wear comfortable sports outfits and indoor sports shoes. Only the double-leg and single-leg stability tests are carried out barefoot.

SEMG electrodes are applied to all participants on the ACL-reconstructed and unaffected legs on gluteus medius and semitendinosus muscles to measure muscle activation throughout the whole test battery.

After block randomization to determine the group, participants complete the test battery as presented in Table 2. For fatigue reasons, the unaffected limb is only tested in the first run. The best performance from each trial is selected for analysis.

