**Hypothesis** **2:**
*Muscle activity of the gluteus medius and semitendinosus muscles is impaired in the ACL-reconstructed leg during the modified BIA test battery.*

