## 4. Data Analysis and Planned Statistical Analysis

All data are presented in a descriptive manner, including anthropometric data and absolute measured values. Side-to-side differences are calculated for all SL tests, using the limb symmetry index (LSI). Therefore, absolute values of the ACL-reconstructed leg are divided by the values of the unaffected leg and multiplied by 100. For the stability, quick feet and speedy tests LSI is calculated by dividing the measured value of the unaffected leg by the value of the ACL-reconstructed leg and multiplied by 100 according to the calculation done in the study by Herbst et al. [17].

Power is quantified in the sagittal plane and defined through force and velocity. This parameter is directly extracted from the force plate data and reported as extracted. It is assessed for jumping during loading phase and total jump height. Power is based on peak power calculations for the lower extremity, which is defined in newton for maximal applied force during contraction. Additionally, it will be interpreted in the context of recent LSI-papers.

Descriptive quantitative data are calculated as the mean ± standard deviation. The Kolmogorov-Smirnov test is used to test the normality assumption. To compare the variances across the means of the three groups we use ANOVA repeated measures. Wilcoxon and Friedman-Test are used as well to calculate between-group differences.

All statistical analyses are performed using SPSS (IBM SPSS Statistics, New York, NY, USA). The significance level for all statistical tests is set a priori to 0.05. A post-hoc power analysis is conducted when significant effects are found.

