## Figures and Tables

**Table 1 healthcare-11-00513-t001:** Individual group test setup.

Run	Group A	Group B	Group C
1	orthosis	brace	no aid
2	brace	no aid	orthosis
3	no aid	orthosis	brace

**Table 2 healthcare-11-00513-t002:** Description of the planned consecutive activities during the measurement session [17,35].

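### For the single-leg tests, a same-run comparison of the two legs without an aid exists only in group C, so LSI and single-leg sEMG carry a device effect or a run lag in groups A and B

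*Protocol article*

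**What the plan says.** Section 2.3 sets the schedule: "The examination is performed in a single session, including three runs of the modified BIA test battery". It then restricts the reference leg: "For fatigue reasons, the unaffected limb is only tested in the first run".

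Table 1 gives the condition by run for groups A, B and C in that order: "1 orthosis brace no aid", then "2 brace no aid orthosis", then "3 no aid orthosis brace".

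Section 4 plans an LSI for every single-leg test, in which "absolute values of the ACL-reconstructed leg are divided by the values of the unaffected leg and multiplied by 100"; the ratio is inverted for the stability, quick feet and speedy tests. It does not name the run or device condition that supplies the operated-leg value. The planned tests compare the three conditions, and no run term is mentioned.

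Hypothesis 2 is also a contrast between limbs: "Muscle activity of the gluteus medius and semitendinosus muscles is impaired in the ACL-reconstructed leg during the modified BIA test battery". The objectives list persisting side-to-side imbalance at six months as a question the trial is to answer.

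**The concern.** An LSI is meant to isolate the difference between the legs, so both should be measured in the same state. Here the reference leg is always a run-1 measurement, while the operated leg is measured in all three runs and under all three conditions. Table 1 balances devices over runs for the operated leg, but it cannot balance device or run between the legs.

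At stake is the answer on residual imbalance. A device effect, or a change in performance over the session, could be reported as a limb deficit or could hide one. A later analysis plan can adjust for this, but it cannot create a same-run, no-aid reference value for groups A and B.

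**Working it through.** The plan states no figure for the limb comparison, so there is none to reproduce.

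**Inputs.** Condition by run: Table 1. Reference leg in run 1 only: Section 2.3. N = 28: Section 2.2. Allocation is read from Section 2.1 as 1:1:1, so each group has 9 or 10 patients. Assumed, because the text does not say: only the operated leg wears the device.

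**Step 1: who gives a clean comparison.**

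| Group | Run 1 | Run of the no-aid test | Lag behind the reference leg |
|---|---|---|---|
| A | orthosis | 3 | 2 runs |
| B | brace | 2 | 1 run |
| C | no aid | 1 | 0 |

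In a device run in run 1: 28 − 10 = 18 (64%) or 28 − 9 = 19 (68%). Clean same-run, no-aid pairs: 10 or 9.

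**Step 2: mean lag of a no-aid LSI.** With 10/9/9 patients: (10×2 + 9×1 + 9×0)/28 = 29/28 = 1.04 runs. With equal groups it is exactly 1.

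**Step 3: what the shift could be.** The documents give no effect sizes. Assume a true LSI of 90, a device effect of ±5% on the operated leg, and a run effect of ±3% per run.

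- Run-1 LSI: the device effect enters in two of three groups. Mean = 90 × (1 ± 0.05 × 2/3) = 87.0 to 93.0. There is no run lag.
- No-aid LSI: the run effect enters with a mean lag of 1. Mean = 90 × (1 ± 0.03) = 87.3 to 92.7, a shift of ±2.7 points. With a 3% decline per run, A is 90 × 0.94 = 84.6, B is 90 × 0.97 = 87.3 and C is 90. There is no device effect.
- LSI pooled over all runs: both enter, giving a mean of 84.4 to 95.8.

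**Step 4: precision of the alternatives.** The unit is the within-person SD, and the target is operated minus unaffected leg at no aid, run 1.

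- Group C only: variance 2/n; with n = 9, SE = √(2/9) = 0.47 (0.45 with n = 10).
- Mixed model on all 28 (random participant; fixed limb, device and run). In a balanced three-by-three square with n per group, the variance is the sum of 1/(9n) for the operated-leg mean, 1/(3n) for the reference leg, 2/(9n) for the no-aid deviation and 2/(9n) for the run-1 deviation. The total is 8/(9n). With n = 28/3 this is 8/84 = 0.095, so SE = 0.31.
- Allowing a leg-specific SD of 1 adds 2/28 for the model and 2/9 for group C: SE √(0.095 + 0.071) = 0.41 against √(4/9) = 0.67.
- The same model with carryover terms, computed numerically from the design with no leg-specific SD: SE about 0.42.

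Carryover matters because after run 1 each condition in Table 1 always follows the same one: brace after orthosis, no aid after brace, orthosis after no aid.

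**The case against.** The strongest reply is that the problem is narrower than it first looks, and most of that reply stands.

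- A reader might infer that all of Hypothesis 2 is compromised. It is not. Section 2.3 has sEMG on both legs throughout the battery, and Table 2 includes double-leg stability, countermovement and drop-jump tests. These record both legs in the same run, so every patient has a same-run, no-aid contrast there.
- A reader might infer that every LSI mixes device and run order. Step 3 shows that a run-1 LSI carries only device and a no-aid LSI only run lag. Both enter only if later device runs are used or runs are pooled, and the article specifies neither.
- A reader might infer that the direction of bias differs by group. For run order the sign is the same in A and B; only the size differs. For devices, the documents do not show opposite effects.
- A reader might take the protocol to predict a decline over runs. Section 2.3 mentions fatigue as the reason for limiting the tests, and the Introduction discusses experience improving repeated jumps in general terms. Neither gives a rate, and they point in opposite directions.
- Group C alone has 56% power (n = 9) or 62% (n = 10) for a paired difference of 0.8 SD, against 98% for 28 pairs. These figures describe an analysis that the protocol does not propose, so they are not the trial's power.
- The sample size is argued from device effects. Those comparisons, made within patient on the operated leg, are not touched: a fixed run-1 denominator cancels in relative terms.

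What the reply leaves standing is the single-leg limb comparison. The schedule is fixed in the protocol, and every way of forming a no-aid or run-1 LSI in groups A and B departs from a like-for-like comparison. Had both legs been braced, the run-1 ratio would compare like with like, but it would not be an unaided imbalance, and the no-aid ratio would then mix device as well as run.

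**Conclusion.** The concern holds for the single-leg LSI and the single-leg sEMG part of Hypothesis 2, and no further. In 18 or 19 of 28 patients the single-leg limb comparison contains either a device effect or a lag of one or two runs. The amount is unknown; the shift of about ±2.7 points on a true LSI of 90 rests on an assumed ±3% per run, and its sign could go either way. The device part rests on the assumption that only the operated leg is braced.

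This should be fixed, but it does not threaten the device comparison. Reference-leg data exist for every patient, and a better analysis is available without changing the schedule. One limit remains under any analysis: where Section 3 fixes the order, the uninjured leg goes first, so limb stays tied to test order within the run.

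**What to change.** - Estimate the single-leg limb difference with a mixed model: random participant; fixed limb, device (on the operated leg) and run. Report the limb contrast at no aid, run 1.
- Repeat it on group C's run-1 data alone as a sensitivity check, and show both estimates with intervals.
- Compare devices on absolute operated-leg values rather than on an LSI with a run-1 denominator.
- State which leg wears the orthosis or brace, and which run and condition feed any LSI that is reported.

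The cost is wording in the analysis section and one sentence in the procedure; no tests are added. The downside is that the model assumes no carryover. Adding carryover terms raises the SE from 0.31 to about 0.42, close to the 0.47 of group C alone, so the assumption should be stated openly.

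Moving the unaffected-leg tests into each patient's no-aid run looks attractive but is not recommended. It would put the extra load into one device condition for everyone and confound Hypothesis 1, whereas the present schedule puts that load in run 1, where Table 1 balances it across conditions.

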### 3.2. Jumps

#### 3.2.1. General Criteria

One practice trial with submaximal power (80% of the maximal power) is given, followed by three subsequent test trialsHands are placed on the hips during the jumpsStarting position in the center of the plate, with feet parallel and shoulder-width apartKnee and hip joints are extended during the flight phaseSoft landing in the center of the 3D force plate with knee over toe position, stable leg axisSingle-leg landing: the contralateral leg is not allowed to touch the ground, otherwise the test is stopped immediately

All tests are explained in detail and demonstrated by the tester. The subject is given time to ask questions about the performance of the jumps. All tests are guided by the same examiner.

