#### 3.3.1. Speedy Jump (SL-SJ)

The patient performs a coordination parkour as quick as possible without breaks. Then, 16 single-leg jumps through a course of red (forward-backward-forward jumps) and blue (sideways jumps) hurdles has to be completed. The hips have to be parallel during the performance. The contralateral leg is not allowed to touch the ground and the limbs are not allowed to touch the hurdle [36]. Time is taken with the stopwatch and the mean value is determined for each course. The sEMG records muscle activation, and 3D movement is tracked by the Azure Kinect DK.

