### 3.6. Biomechanical Measurements

#### 3.6.1. SEMG and MVC

Prior to electrode placement the skin is cleaned and degreased with alcohol. Surface electrodes with a two cm center-to-center distance are attached along the direction of the muscle fibers on the evaluated muscle bellies. The signals are registered with 16-bit accuracy at a sampling rate of 1500 Hz and stored for subsequent analysis using Noraxon DTS unit (Noraxon USA). The EMG signals are filtered with a Butterworth high-pass filter (cutoff frequency 10 Hz) and a low-pass filter (cutoff frequency 500 Hz). The sEMG signal from the evaluated muscles are measured continuously during the modified BIA test battery.

The collected data is normalized to a reference value. Maximum voluntary contraction (MVC) is performed separately for each muscle investigated before the test trials. The MVC contractions is performed against a static resistance. The parameters of each muscle are expressed as a percentage of its MVC (%MVC).

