#### 3.6.3. Motion Capture Camera Setup

We are using the Microsoft Azure Kinect DK, a 3D marker-less motion capture camera system, to track the participant’s maximum valgus and varus knee position during the landing maneuvers. For this study, three cameras capture motion data synchronously at 30 Hz. They are placed in a circle around the subjects with approximately 120° spacing (one frontal view and two back-side views), fixed on tripods 90 cm above the ground and placed approximately three meters from the circle center. The motion capture system is synchronized to the sEMG system and force plate using an illuminated ball controlled by the sEMG software. This ball is placed to be seen by one camera. From the color stream of this camera, we infer the ball’s on and off phases. Subsequently, the synchronization shift is calculated.

The Azure Kinect Body Tracking SDK delivers 3D joint positions and orientations for each joint segment. From this, 3D knee angles are obtained by regarding the left and right ankle, knee, and hip joint positions by calculating the angles between the hip-knee and knee-ankle vectors. Additionally, the local 3D joint segment orientations are used to calculate flexion and extension, abduction and adduction, and internal and external rotation. The resulting kinematic and angular data is filtered using a 4-th-order Butterworth filter with a cutoff frequency of 10 Hz.

Studies show good reliability when using the Azure Kinect for Motion analysis purposes [29]. So far, the Azure Kinect camera has been evaluated for gait analysis and slower functional movements [31]. Although the movement of subjects during the protocol is very fast, especially for the quick feet and countermovement jumps, we are only interested in the maximum varus and valgus knee angles during the landing phase. Therefore, a sampling frequency of 30 Hz is regarded as sufficient as we are not analyzing the entire complex functional movement. For this purpose, the camera would have to be evaluated against a marker-based motion capture system. Furthermore, compared to video camera systems, where only 2D information can be retrieved, the 3D system allows for the calculation of 3D angles and therefore provides more insightful data. Especially this marker-less motion capture offers huge advantages as the time-consuming marker placement can be alleviated and is thus easier to implement in everyday clinical practice.

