**Functional—Biomechanical Assessment**	
1. Stability tests Equipment: Zebris, sEMG Variables: level of stability, center of pressure, muscle activity	[figure not shown] *Picture 1* Double-leg stability test → 1 rep for 10 s Single-leg stability test on the unaffected leg → 1 rep for 10 s Single-leg stability test on the ACL-reconstructed leg → 1 rep for 10 s
2. Jumps Equipment: 3D force plate Bertec, Azure Kinect, sEMG, vaulting box Variables: jump height (cm), power (W/kg), ground contact time (ms), reactivity (mm/ms), muscle activity, knee-angle	[figure not shown] *Picture 2* Double-leg countermovement jump (CMJ) → 3 rep (4 s break in between) Single-leg CMJ on the unaffected leg → 3 rep (8 s break in between) Single-leg CMJ on the ACL-reconstructed leg → 3 rep (8 s break in between) Double-leg drop jump → 3 rep (8 s break in between) Single-leg landing on the unaffected leg → 3 rep (4 s break in between) Single-leg landing on the ACL-reconstructed leg → 3 rep (4 s break in between)
3. Jump coordination Equipment: speedy basic jump set, quick feet jump set, stopwatch, tapping rate counter, sEMG, Azure Kinect Variables: time (s), tapping rate, muscle activity, knee-angle	[figure not shown] *Picture 3* Single-leg speedy jump on the unaffected leg → 1 rep Single-leg speedy jump on the ACL-reconstruced leg → 1 rep Double legged—quick feet test → 1 rep (15 circles, starting with the right leg)
4. Isometric hip abductor strength test (rt/lt) Equipment: sEMG, Expander Variables: strength (N) muscle activity	[figure not shown] *Picture 4* unaffected leg → 1 rep for 5 s ACL-recontructed leg → 1 rep for 5 s

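### The best-performance rule has no usable meaning for sEMG and knee-angle variables, which as written would rest on one of three recorded repetitions picked by an unnamed criterion

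*Protocol article*

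**What the plan says.** Section 2.3 (Procedure) gives one selection rule for the whole battery: "The best performance from each trial is selected for analysis". Section 3.2.1 uses the word trial for a single repetition, so I read the rule as the best of the repetitions of each test.

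For the jumps, Section 3.2.1 says that one submaximal practice trial "is given, followed by three subsequent test" trials. Table 2 agrees, listing three repetitions for every jump and landing. Its entry for this block reads "Variables: jump height (cm), power (W/kg), ground contact time (ms), reactivity (mm/ms), muscle activity, knee-angle", so muscle activity and knee angle sit in the same list as the performance measures. Section 3.6.1 adds: "The sEMG signal from the evaluated muscles are measured continuously during the modified BIA test battery". On knee angle, Section 3.6.3 says "we are only interested in the maximum varus and valgus knee angles during the landing phase".

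For the speedy jump, Section 3.3.1 says "Time is taken with the stopwatch and the mean value is determined for each course", while Table 2 has "Single-leg speedy jump on the unaffected leg → 1 rep" and likewise one repetition on the reconstructed leg.

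**The concern.** The rule suits a maximal-effort score, but the article applies it to everything that is analysed. Muscle onset, time to peak and percentage of MVC have no best value. Even among the four performance variables of the jumps, different ones can pick different repetitions, and none is named as the selector.

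The single-leg landing (Section 3.2.5) shows the difficulty most clearly. The patient steps off a box, lands on one leg and holds for five seconds, so there is no jump height to rank. A stable leg axis is part of the standard for a proper landing (Sections 3.2.1 and 3.2.5). If best means the most stable landing, selection acts directly on valgus, the outcome of Hypothesis 4. If it means something else, the choice of landing is arbitrary with respect to valgus.

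Hypotheses 2 to 4 depend on these variables. There are 28 patients, and the unaffected limb is tested only in the first run (Section 2.3), so its side of a limb contrast in a given jump could rest on one repetition per patient. An unnamed selector also leaves open, at analysis, which of three repetitions supplies each patient's value.

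**Working it through.** **Plan's own figure.** There is none on this point. The article states no SD, ICC or trial-to-trial variance for any variable. The required sample size of 27 (Section 2.2) rests on an unquantified large effect and contains no repetition-level variance. It is used only in step 4, as a reference n.

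**Inputs from the article.** Three repetitions per jump or landing (Section 3.2.1, Table 2); one repetition for the stability, speedy jump, quick feet and strength tests (Table 2); alpha 0.05, power 0.90, n = 27 (Section 2.2).

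**Assumption that is varied.** Let t be the share of the variance of a single-repetition contrast (device or limb) that is trial-to-trial noise. I take t = 25%, 50% and 100%. Repetitions are treated as independent with equal variance.

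**Step 1: one repetition against the mean of three, sEMG or valgus.** If the retained repetition is chosen on a variable uncorrelated with the one analysed, it behaves as a single random repetition, with relative variance 1. The mean of three has variance (1 − t) + t/3.

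| t | Variance of mean | SE ratio, mean to single | SE reduction | Equivalent N |
|---|---|---|---|---|
| 25% | 0.75 + 0.083 = 0.833 | √0.833 = 0.91 | 9% | 1/0.833 = 1.2 |
| 50% | 0.50 + 0.167 = 0.667 | √0.667 = 0.82 | 18% | 1/0.667 = 1.5 |
| 100% | 0.333 | √0.333 = 0.58 | 42% | 1/0.333 = 3.0 |

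**Step 2: the selector is correlated with the analysed variable.** With normal noise, the best of three has variance 0.56 and expected value 0.85 trial SDs above the mean (simulated, 2 million triples). For within-patient correlation r between selector and analysed variable, the noise variance of the retained value is 0.56r² + (1 − r²), and its expected shift is 0.85r.

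- r = 0: variance 1.00, shift 0.
- r = 0.3: variance 0.96, shift 0.25.
- r = 0.6: variance 0.84, shift 0.51.

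The two harms therefore trade off. At r = 0 the precision loss is largest and selection creates no dependence on performance. As r grows the loss shrinks somewhat, but the valgus or sEMG value becomes shifted by the selection.

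**Step 3: best of three for the selecting variable itself, such as jump height.** Under normal noise the SE of the mean relative to that of the best of three is √[((1 − t) + t/3) / ((1 − t) + 0.56t)], that is 0.97, 0.93 and 0.77 for t = 25%, 50% and 100%. This depends on the noise being symmetric. If attempts fall short of capacity one-sidedly, for example noise = −Exp(1), the best of three has variance 1/9 = 0.11 and the mean 1/3 = 0.33, so the order reverses.

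**Step 4: in terms of detectable difference.** With a normal approximation and a paired contrast, (1.96 + 1.28)/√27 = 0.62 single-repetition contrast SDs for one repetition. Multiplying by the SE ratios of step 1 gives 0.57, 0.51 and 0.36 for the mean of three at t = 25%, 50% and 100%.

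**Step 5: speedy jump.** With one repetition per leg, best, mean and the single value are the same number. Section 2.3 (best), Section 3.3.1 (mean) and Table 2 (one repetition) conflict in wording, with no effect on precision.

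**The case against.** The strongest reply is that Section 2.3 speaks of performance. A reader might infer that the plan throws away sEMG and knee-angle data from two of every three jumps, but no section says so. sEMG runs continuously, and the Introduction refers to a cumulative dynamic valgus during landings. Repetition-level signal processing is also something a condensed article may leave to the full plan. This stands as far as it goes: discarding is the natural reading of an unqualified rule, not an explicit statement. What remains is that the one rule the article does state cannot be applied to these variables.

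A reader might also infer that valgus is read from the landing after the highest jump. Jump height is nowhere named as the selector. The single-leg landing has no jump to rank, and in the drop jump the first landing comes before the jump.

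A third tempting reading is that best of three is wrong for jump height or power. It is not. The countermovement and drop jumps call for maximal effort, best of three draws on all three attempts, and the mean answers a different question (typical rather than maximal performance). Step 3 shows that the mean's precision advantage is modest for smaller noise shares and reverses under one-sided noise. This part of the reply stands in full.

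Finally, the size of the loss cannot be derived from the article. That is correct, and it is why only a range is given.

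**Conclusion.** The concern holds in a limited form. For the tests with three repetitions, the article fixes a selection rule that is undefined for sEMG and, for maximum valgus, either acts on the endpoint or is arbitrary. If the rule is followed as written and the repetition is chosen on an uncorrelated variable, averaging would lower the SE of sEMG and valgus contrasts by about 9% to 42%, equivalent to 1.2 to 3.0 times the patients. That range rests on assumed noise shares of 25% to 100% and on independent repetitions of equal variance. The documents do not show where in the range this trial lies.

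The finding does not extend to best of three for maximal performance outcomes or to the tests with a single repetition. The speedy-jump conflict is one of wording only.

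**What to change.** - For the three-repetition jump and landing tests, state that sEMG and knee-angle variables are analysed as the mean of the valid repetitions per leg and run.
- Keep best of three for maximal performance outcomes such as jump height and power, and name for each test the variable that defines best.
- Reconcile Sections 2.3 and 3.3.1 with Table 2 for the speedy jump: if one repetition stands, say that the single recorded time is analysed and remove the reference to a mean.

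The cost is extra processing of signals that are already recorded. No further testing, patients or visits are needed, and the jump performance outcomes keep the best-of-three rule that the article already has.
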